## Abstract

**Background:**

A secure attachment with one or more caregivers is one of the most important predictors of cognitive development and emotional wellbeing. Persons with intellectual disabilities (ID) have extra need for secure relationships with primary caregivers but can find making connections difficult. This study aims to explore the effect of a non-invasive m-learning intervention on the empathy and self-efficacy of caregivers, in view of improving attachment relationships with persons with ID.

**Methods:**

A randomized controlled trial (RCT) will be conducted to assess the efficacy of the HiSense APP-ID. The study will include 100 parents/relatives and 100 professional caregivers of adults with mild or moderate ID (18 years and older). Of both groups of participants, half will complete the m-learning intervention. Data will be collected before the intervention starts, immediately after completion of the m-learning, and 1 month after the intervention. Participants will complete questionnaires concerning knowledge about attachment theory, empathy and self-efficacy (primary outcome measures) and social validity (secondary measures).

**Discussion:**

The intervention aims to increase caregiver understanding of attachment theory and to improve empathy and self-efficacy, which may lead to better care and less stress in social interactions. The HiSense APP-ID is an m-learning intervention that can be done independently on any digital device. The course is therefore easily accessible for caregivers of persons with ID. The current study will provide insight into the effectiveness of the intervention for parents/family members and professional caregivers of persons with mild or moderate ID.

**Trial registration:**

Nederlands Trial Register, NTR 6944. Registered on 16 December 2017.

**Electronic supplementary material:**

The online version of this article (10.1186/s13063-018-2772-7) contains supplementary material, which is available to authorized users.

## Background

A secure attachment with one or more caregivers is one of the most important factors in cognitive and emotional development. Persons with intellectual disability (ID) may remain dependent on a caregiver for various aspects of their lives, often including coping with emotions and stress. It is therefore crucial that parents and other caregivers of persons with ID are aware of their responsibilities in establishing a secure relationship and that they know how to support the emotional development of their loved one or client.

Children and their parents often form an attachment relationship, but other family members also can be involved, as can a caregiver at daycare or a teacher at school [1, 2]. The attachment figure alternately serves as a secure base and a safe haven: by functioning as a secure base, the attachment figure encourages a child to explore the world within safe boundaries. By providing a safe haven, the attachment figure gives the child assurance of available comfort in moments of distress [3–5]. A well-balanced presentation of these two aspects will support the emotional development of the child. Furthermore, the quality of an attachment relationship greatly depends on a caregiver’s sensitivity for the communicative signals of the other person. Equally important is an adequate response to these signals [4–6]. Depending on the sensitivity and responsiveness of the attachment figure, the child develops a general internal working model regarding confidence in the caregivers [7]. A child with secure attachments feels safe and confident in the interaction with others [8], and conversely, insecure attachment may lead to problematic coping strategies in children [9]. Parents and other caretakers are essential in teaching the child to apply appropriate coping strategies. Children with insecure attachment tend to display problematic behavior within social relationships and in dealing with stressful situations in daily life [10, 11].

Persons with ID may continue to need this type of guidance throughout their lives. Difficulties in information processing can present an obstacle to understanding social situations. Consequently, persons with ID are more likely to encounter situations they find overwhelming and stressful and in which they need attachment figures to assist in emotion regulation [9]. At the same time, parents and other caregivers may experience more difficulties in establishing a secure relationship with a child or adult with ID than with a typically developing person [12]. Janssen, Schuengel, and Stolk have listed four relevant main factors that can increase risk of insecure attachment [9]. First, parents may have difficulty accepting their child’s diagnosis, causing stress and limiting their sensitivity to any signals of stress or discomfort. Second, the communication skills of persons with ID are generally weak, which can lead to misinterpretation of their signals and behavior. Third, persons with ID may struggle to master the skills that are typically considered prerequisites for developing an attachment relationship, such as object permanence and distinguishing cause and effect. Fourth, persons with ID will often encounter a variety of caretakers at home and school and during other daily activities, which can be a source of stress. Some children and many adults with ID spend time in residential care where the availability of caretakers is limited or irregular, which is disruptive for the attachment relationship with their parents or other primary caregivers [13, 14].

Sensitivity and responsiveness correlate with an ability to understand someone else’s needs and emotions [15–17]. Empathy, which can be defined as the ability to tune into how the other person is feeling [18], is crucial in the development of a secure attachment style in children. Empathic behavior in parents is positively related to the attachment security and emotional openness of children [19]. Moreover, recent research by Settipani and Kendall [20] showed that higher levels of empathy allow mothers to estimate their child’s ability to face feared situations at a particular moment, a skill that is crucial in discerning when the child benefits most from a safe haven (providing comfort in times of distress) or a secure base (encouraging independence). Among medical professionals, empathy is positively linked to treatment outcomes, but this population shows a decline in empathy over time [21, 22].

In addition, self-efficacy can be an important factor in the behavior of parents and professional caregivers towards a person with ID [23]. For parents, a major source of experienced stress is their assessment of the situation and the various available support resources [24]. Parents who feel in control of the situation and are confident in their own parenting skills report lower stress levels than parents who do not feel that they can influence their child’s behavior [25]. A high level of parental stress may undermine parent sensitivity and responsiveness towards their son or daughter. Studies have shown that interventions based on attachment theory can boost self-efficacy in parents and induce attachment-related behavior between parents and their child [26, 27].

In short, improving the empathy and self-efficacy of caregivers may reduce stress in the home environment and, as a result, boost the cognitive and emotional functioning of the child. Various interventions have been developed to optimize attachment relationships between children and caregivers [26–29]. Bakermans-Kranenburg, van IJzendoorn, and Juffer [30] found that short interventions with a clear behavioral focus on enhancing parental sensitivity were the most successful in improving secure attachment in infants. Furthermore, Schuengel, De Schipper, Sterkenburg, and Kef [31] conclude in a summary of available research that interventions focusing on insight into attachment behaviors and relationships are most likely to stimulate the development of attachment relationships in persons with ID.

### Rationale

The present m-learning intervention aims to educate parents and caregivers and encourage reflection on the interaction with their adult child or client. The intervention aims to increase empathy by providing new information or refreshing their memory about the inner world of persons with ID. In addition, participants learn how to improve their sensitivity and responsivity through theoretical insights and practical examples. An increase in theoretical and practical knowledge enhances awareness in caregivers of their role in establishing a secure relationship with their child or client and increases their sense of self-efficacy.

The present intervention offers small quantities of theoretical and practical knowledge in an m-learning course that requires only 5 min each day over a period of 30 days. Each day, participants answer four multiple-choice questions and receive feedback. This approach allows active involvement in the learning process by giving the user the opportunity to think about answer alternatives. At the same time, the questions can be answered quickly enough to fit in the busy schedule of parents and professional caregivers.

In short, the study aims to explore the effects of the HiSense APP-ID intervention on the empathy and self-efficacy of parents/relatives and professional caregivers of persons with mild or moderate ID.

### Hypotheses

The intervention is hypothesized to have positive effects on the basic knowledge about attachment theory and to increase empathy and self-efficacy in parents/relatives and professional caregivers of persons with mild or moderate ID.

#### Primary hypotheses

The primary hypotheses are:Participation in the intervention will be associated with an increase in theoretical knowledge about sensitive and responsive interaction, for both parents/relatives and professional caregivers.Participation in the intervention will be associated with an increase in empathy and self-efficacy, for both parents/relatives and professional caregivers.

#### Secondary hypothesis

The secondary hypothesis is that parents/relatives and professional caregivers will experience the intervention as a pleasant and challenging way to gain theoretical knowledge.

## Methods

### Study design

The effect of the HiSense APP-ID will be assessed in two separate two-group, parallel, single-blinded randomized controlled trials (Fig. 1). Parents and close family members are treated as one group and professional caregivers as another group. Each group will be analyzed separately.

**Fig. 1 Fig1:**
[figure not shown]
Timeline of the randomized controlled trial. This procedure will be followed separately for the two groups (parents/relatives and professional caregivers)

We report the methods of this study according to the Standard Protocol Items: Recommendations for Interventional Trials (SPIRIT) Checklist (see Additional file 1).

Questionnaires on empathy and self-efficacy will be completed at three time points: at T0, before the intervention starts; at T1, when the intervention is finished; and at T2, when a retention measurement will be taken 30 days after the intervention (Fig. 2).

**Fig. 2 Fig2:**
[figure not shown]
Schedule of enrollment, allocation, intervention, and assessments

### Sample size

The sample size is estimated for linear mixed effects modeling with two conditions, three repeated measures, and clustered data. Based on a pilot study among caregivers in a care center, means and standard deviations can be estimated for empathy, self-efficacy, and knowledge. The desired power is set to a minimum of 0.90 and α = .05. The three care centers are taken into account as clusters with intra cluster correlation of .2. We estimate that around 90 participants are needed to detect a main effect of 0.5 SD on the primary outcome measures. To correct for attrition, we increased the highest number by 10%, bringing the total number of participants to 100 parents/relatives and 100 professional caregivers.

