### Recruitment

The study will include two samples. The participants will be 100 professional caregivers and 100 parents/relatives of adults with mild or moderate ID (intelligence quotient (IQ) 35–70). This also included persons with ID and additional psychiatric diagnoses such as autism spectrum disorders, or additional physical disabilities such as a visual impairment. The group of professional caregivers will be recruited within three Dutch centers providing care for persons with ID living in group homes. Each care center has multiple group homes and activity centers in The Netherlands. The group of parents/relatives of adults with mild or moderate ID will be recruited from these and other centers throughout The Netherlands. Close relatives, such as a brother, sister, uncle, or aunt, can participate if the parents of a client are no longer the primary caregivers.

Participants in both samples will be recruited and enrolled by the participating care centers, which combined are connected to 3107 professional caregivers and 4830 parents/relatives. Participants will be invited to participate when they care for one or more persons with mild or moderate ID.

Candidates will be excluded from participation when they primarily care for persons with severe intellectual disability (IQ below 35) or when their use of HiSense APP-ID will be interrupted for more than five consecutive days. For parents/relatives, only one family member per client is included.

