### Randomization

Cluster randomization among locations of the care centers will be used to prevent crossover effects between professionals and parents/relatives. Group homes and activity centers will be randomly assigned to the treatment condition or the care-as-usual condition by an independent party, based on order of entry and a pre-determined order of treatment conditions. Randomization of participants will occur after enrollment but before the baseline assessment. Participants are to be informed of their allocated condition shortly after T0 to reduce any response bias during the baseline assessment.

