#### Empathy (T0, T1, T2)

The Empathy Quotient (EQ) questionnaire [18] (Dutch translation by De Corte and Uzieblo [37], adapted by Volman [38]), contains 60 items with a 4-point Likert scale. Participants indicate their level of agreement with statements regarding their sensitivity in social contexts. This study will use the abridged version of 40 items [18]. The EQ has high test–retest validity (*r* = .97, *p* < .001) and high internal consistency [39] (α = .92).

The Interpersonal Reactivity Index [40] (IRI) contains 28 items, divided over four subscales (perspective taking, fantasy, empathic concern, and personal distress). Participants indicate on a 5-point Likert scale how well each statement describes them. All subscales have sufficient internal reliability (.71–.77) and test–retest reliability (.62–.72).

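### The stated power of at least 0.90 counts the three care centers as the clusters, but group homes and activity centers are randomised, so the figure does not reflect the design

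*Protocol article*

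**What the plan says.** The Sample size section describes a calculation for "linear mixed effects modeling with two conditions, three repeated measures, and clustered data". It sets the targets ("The desired power is set to a minimum of 0.90 and α = .05"), names the cluster level ("The three care centers are taken into account as clusters with intra cluster correlation of .2") and concludes: "We estimate that around 90 participants are needed to detect a main effect of 0.5 SD on the primary outcome measures". Adding 10% for attrition gives 100 in each sample.

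The Randomization section states: "Cluster randomization among locations of the care centers will be used". The units allocated are group homes and activity centers. The Recruitment section says that each care center has several of these. According to the Procedure section, professionals are recruited as groups of colleagues from the same home or activity center. Parents/relatives "will be recruited from these and other centers throughout The Netherlands".

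The Data analysis section gives random intercepts for participant and care center, and none for location.

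**The concern.** In a cluster-randomised trial, power is governed by the correlation among people who share a randomised unit. Here that unit is the location. Both conditions can occur within a care center, so a center intercept takes center differences out of the comparison. An ICC placed at center level therefore lowers the required number, whereas an ICC at location level raises it. The calculation appears to have dealt with clustering, but it has dealt with a kind that does not harm the comparison and left out the kind that does.

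The three-center description also does not fit the parents/relatives, who may come from other centers, yet the same number is used for them.

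If the result is null, readers will interpret it against a claimed power of at least 0.90 that was not worked out for the design as randomised.

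**Working it through.** **Inputs from the protocol article.** Effect 0.5 SD, power 0.90, α = .05 (two-sided assumed), equal arms, N = 90 before attrition, three measures, center ICC .2. The article gives no within-person correlation r for sizing. Its only over-time correlations are test–retest values in the Empathy section: .97 for the Empathy Quotient, and for the Interpersonal Reactivity Index "sufficient internal reliability (.71–.77) and test–retest reliability (.62–.72"). These are instrument properties and are used here only as a plausible range.

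**Base number.** Total N = 4(1.960 + 1.282)²/0.5² × f = 168.1 × f, where f is the variance of the analysed summary relative to a single measure.

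**The plan's own figure.** With the mean of three measures and center ICC .2 removed as a stratum, f = (r − .2) + (1 − r)/3.

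| r | f | N for 0.90 |
|---|---|---|
| .60 | 0.533 | 89.7 |
| .62 | 0.547 | 91.9 |
| .72 | 0.613 | 103 |
| .97 | 0.780 | 131 |

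So about 90 can be recovered at r near .60, with the center ICC reducing the number. Attrition agrees with the stated 100: 90 × 1.1 = 99 and 90/0.9 = 100.

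**Randomised locations as clusters.** Assumptions: m participants per location, ICC .2 moved from center to location level, N = 90, t-test with 90/m − 2 degrees of freedom, noncentrality 0.5 × √(90/(4f)).

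- Main effect over three measures: f = .2m + (r − .2) + (1 − r)/3. For m = 5 and r = .62, f = 1.0 + .42 + .127 = 1.547.
- T1/T2 mean adjusted for T0, with the location ICC persisting after adjustment: f = [(1 + r)/2 − r²] × [1 + (m − 1) × .2]. For m = 5 and r = .62, f = 0.4256 × 1.8 = 0.766.

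| m | Main effect: power at r = .62 / .72 | T0-adjusted: power at r = .62 / .72 |
|---|---|---|
| 2 | 0.66 / 0.63 | 0.90 / 0.95 |
| 3 | 0.57 / 0.55 | 0.84 / 0.91 |
| 5 | 0.43 / 0.42 | 0.72 / 0.81 |
| 8 | 0.31 / 0.30 | 0.56 / 0.65 |

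**A smaller location ICC.** With .05 in place of .2, main-effect power is 0.70 to 0.67 at m = 3 and 0.63 to 0.60 at m = 5.

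**A stable location effect that T0 removes.** Analyse location means and adjust for the location's T0 mean. For m = 5 and r = .62, the T0 variance is .2 + .8/5 = .36, the covariance .2 + .42/5 = .284 and the T1/T2 variance .2 + (.42 + .19)/5 = .322. The residual is .322 − .284²/.36 = .098, so f = 5 × .098 = 0.49 and power is 0.89. At r = .72 power is 0.95. For m = 8 the pair is 0.84 and 0.92.

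**The case against.** The strongest reply is that the low figures rest on three things the article does not give: location size, location ICC and within-person correlation. A condensed article may leave such inputs to the full protocol. Under T0 adjustment, 0.90 can be reached with very small locations, a low location ICC, a high r, or a location effect stable enough for T0 to remove. For parents/relatives, only one family member per client is included, and nothing supports locations of 5 to 8 or an ICC of .2 in that sample. All of this stands. It limits how large the loss can be said to be. It does not rescue the stated basis, because the article does name its cluster level, and that level is not the one randomised.

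Three stronger readings are tempting and are not supported:

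- **That about 90 is an arithmetic error.** Ignoring the center term, 90 would require a lower within-person correlation than the test–retest values suggest. But the plan does include that term, and with it r near .60 gives 90. Since no r is stated for sizing, the figure cannot be checked from the article's inputs. It is not shown to be wrong on its own terms.
- **That the design effect should be computed with the three centers as randomised units.** The Randomization section allocates locations, so such a calculation describes a design that nobody proposes.
- **That high test–retest correlation always means too little power.** It raises the number needed for a main effect over three measures. With T0 adjustment it lowers it: before location clustering, r = .62 to .72 needs 168.1 × 0.4256 to 168.1 × 0.3416, that is 72 to 58 participants.

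**Conclusion.** Wrong as written. The claimed minimum of 0.90 belongs to a model with clustering by care center, whereas the trial randomises locations within centers, and correlation within locations appears in neither the sample size nor the analysis model. This conclusion follows from the text and needs no assumption.

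Its size does depend on assumptions. With ICC .2 at location level, r of .62 to .72 and N = 90, power at 3 to 8 participants per location is roughly 0.57 down to 0.30 for the three-measure main effect. For the T0-adjusted contrast with that ICC persisting, it runs from 0.91 down to 0.56. A reader might infer that the trial is certainly underpowered. The documents do not establish that, since favourable but possible conditions bring the T0-adjusted power to 0.90 or above. They establish that 0.90 has not been justified for this design.

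**What to change.** Keep 100 plus 100. In the Sample size section, replace the sentence containing "The desired power is set to a minimum of 0.90" with the power, or the detectable difference, and its range. Compute it for location-randomised clusters from the planned number and mean size of locations, a location-level ICC and a stated within-person correlation. Use the T0-adjusted T1/T2 contrast. Do this separately for professionals and for parents/relatives, whose centers are not limited to the three. Include location in the analysis model that the calculation assumes, so that the two agree.

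The cost is revised text and probably a less favourable power figure, with no additional participants. Spreading the professionals over more locations would raise power, but it is not free: researchers visit residences with a laptop for each measurement, and colleagues are recruited as groups.

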### Recruitment

The study will include two samples. The participants will be 100 professional caregivers and 100 parents/relatives of adults with mild or moderate ID (intelligence quotient (IQ) 35–70). This also included persons with ID and additional psychiatric diagnoses such as autism spectrum disorders, or additional physical disabilities such as a visual impairment. The group of professional caregivers will be recruited within three Dutch centers providing care for persons with ID living in group homes. Each care center has multiple group homes and activity centers in The Netherlands. The group of parents/relatives of adults with mild or moderate ID will be recruited from these and other centers throughout The Netherlands. Close relatives, such as a brother, sister, uncle, or aunt, can participate if the parents of a client are no longer the primary caregivers.

Participants in both samples will be recruited and enrolled by the participating care centers, which combined are connected to 3107 professional caregivers and 4830 parents/relatives. Participants will be invited to participate when they care for one or more persons with mild or moderate ID.

Candidates will be excluded from participation when they primarily care for persons with severe intellectual disability (IQ below 35) or when their use of HiSense APP-ID will be interrupted for more than five consecutive days. For parents/relatives, only one family member per client is included.

